### Randomization to the treatment arm

The original plan for randomizing participants was to randomize each couple to either the active or control condition immediately after both members of the dyad completed the baseline assessment using a stratified randomization scheme within blocks of four. After the trial launch in August 2017, we quickly encountered substantial difficulty in randomizing at the couple level; because the first two sessions of the interventions occur in groups, a large enough number of couples would need to complete baseline within the same timeframe, and these couples’ schedules would all need to align in order to convene group sessions. Because of this, we altered the randomization strategy to randomize at the group level. To achieve this, each couple provides their availability for a set of pre-scheduled group sessions occurring over the subsequent 3 months. Once at least two couples sign up for a group session (six couples maximum), all couples within that group are randomized to the active or control condition. All couples must attend their first group session within 3 months of completing their baseline assessment. Participants who do not attend their first session within 3 months are required to re-complete their baseline assessment; otherwise, they are no longer eligible to be enrolled.

To randomize at a group level, we adopted a more flexible covariate-adaptive randomization method known as Minimization [40, 41] on January 16, 2018, after 10 couples had been randomized using the prior approach. Minimization effectively addresses the scheduling difficulties inherent in couple-level block randomization by allowing sequentially recruited clusters of couples (e.g., 4–12 individuals) to be treated as single units, while offsetting imbalance in both individual- and couple-level prognostic variables [42]. Compared to stratification, Minimization can handle a larger number of prognostic factors and is more efficient in controlling imbalance in baseline variables than simple or restricted randomization [43]. In this trial, we set the biasing probability to 0.80 and used the range as the metric of imbalance in the minimization functioning.

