### Interventions

#### 2GETHER (active)

2GETHER is comprised of four sessions. First, couples complete two in-person group sessions aimed at skills building, which totals approximately 6.5 h of content. These group sessions address communication skills, coping with stress (both general and sexual minority-specific stress), relationship sexual satisfaction, and HIV transmission risk within the dyad and with outside partners. Two facilitators reinforce core concepts of the intervention through structured conversations about how skills apply to couples’ relationships. In-person groups are attended by 2–6 couples; if a couple does not show up to a group session, we proceed with the session and conduct a make-up session with the missed couple. In rare cases, couples may proceed with the intervention without having completed a make-up session (i.e., if their schedule does not allow), but in these cases, we incorporate missed content into the remaining sessions.

Following the two group sessions, each couple completes two individualized in-person skills coaching sessions (with no other couples attending) with one facilitator, aimed at skills implementation. The first skills coaching session focuses on communication skills and problem-solving. Couples discuss up to two areas of disagreement in session; each partner communicates concerns, actively listens to their partner, and discusses problem-solving, with guidance and corrective feedback from the facilitator to improve the use of these skills. The second skills coaching session, and the zenith of the intervention, focuses on sexual health. Utilizing effective communication skills, couples discuss sexual satisfaction within the dyad, their preferences for a monogamous or non-monogamous relationship agreement, and biomedical and behavioral HIV prevention strategies. HIV-positive participants and HIV-negative participants on PrEP receive medication adherence counseling, based on the Life-Steps protocol [44]. At the end of the sexual health skills coaching session, couples draft a detailed relationship agreement, which includes specific rules about monogamy or non-monogamy and HIV prevention practices. After establishing an agreement, the couple discusses strategies for maintaining or altering the agreement in the future, as well as how they will handle agreement breaks if they occur.

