#### Analyses of primary aims

Imbalances in key stratification variables in baseline data that were not addressed via randomization will be adjusted for in the analyses of treatment effects. Analysis of variance and chi-square tests will be employed to identify those baseline differences on prognostic variables, like age discordance and couple HIV status, the main study outcomes, and demographic variables.

Cochran-Mantel–Haenszel tests of two independent binomial proportions will be used to detect differences in the STI prevalence rates, our primary biological outcome, from baseline to 12-month follow-up. Our main behavioral outcome is condomless anal sex with serodiscordant or unknown status partners. In order to account for the nested nature of dyadic data, we will assess outcome, as well as our secondary outcomes, with multilevel latent growth modeling. Data from all four of our follow-up surveys (3, 6, 9, and 12 months) will be incorporated into those growth models. The treatment condition will be used as a dyad-level predictor within the multilevel framework that will predict differences in intercept and slope terms. This method will not only detect differences in change over time by the treatment condition predicting slopes, but we will also detect differences at each follow-up time point by shifting the intercepts from 3-month to 6-, 9-, and 12-month follow-up.

Indicators of relationship functioning will be tested as mediators of significant differences between the two study arms on the primary outcomes. We will employ Fritz’s [56] approach for testing longitudinal mediation in latent growth models. This is a parallel process approach where the mediator is treated as a lagged effect to maintain the temporal order of events between the mediator and the outcome. A percentile bootstrap test will be used to determine the indirect effect of treatment on the outcome through the lagged mediator.

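### Whole session groups are randomized, but the growth models enter treatment at the dyad level with no group term, so standard errors are too small if couples in a group are positively correlated

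*Protocol article*

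**What the plan says.** Under Randomization to the treatment arm, the Protocol article reports that couple-level block randomization proved impractical and that "we altered the randomization strategy to randomize at the group level". The change took effect on January 16, 2018, "after 10 couples had been randomized using the prior approach". A group needs at least two and at most six couples, and then "all couples within that group are randomized to the active or control condition". Minimization was chosen partly for "allowing sequentially recruited clusters of couples (e.g., 4–12 individuals) to be treated as single units".

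Under 2GETHER (active), the first two sessions are group sessions: "In-person groups are attended by 2–6 couples". The PEONY section describes the same hybrid of group and couple sessions. Under Protocol changes after trial launch, couples who could not make the next three scheduled cohorts could be randomized as a group of one. The number of such couples is not given.

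Under Analyses of primary aims, the behavioural primary outcome and the secondary outcomes are analysed by multilevel latent growth models, chosen because of the dyadic nesting: "The treatment condition will be used as a dyad-level predictor within the multilevel framework". The article mentions no group random effect, group-robust variance or other group-level adjustment.

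**The concern.** In every group of two or more couples, treatment does not vary between the couples. It is a group-level variable, and the model as described fits the couple-level design that was dropped after 10 couples.

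Some positive correlation between couples in a group is plausible. They are brought together by shared availability, enter in the same calendar period (which for some spans the move to remote delivery in March 2020), and attend two facilitated group sessions together. With such a correlation, a dyad-only model understates the variance of the treatment effect and credits the test with too many independent units. That bears on the primary behavioural outcome and on the secondary outcomes analysed the same way.

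**Working it through.** **1. Reproduce the plan's own power.** Inputs from Power analysis: J = 125 dyads, n = 2 per dyad, within-couple correlation 0.5. Assumed, because not stated: two-sided alpha 0.05, equal allocation, medium d = 0.5, large d = 0.8.

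- Noncentrality = √(J·d² / (4·ICC + 4·(1−ICC)/n)), with J − 2 = 123 degrees of freedom. The denominator is 4(0.5) + 4(0.5)/2 = 3.
- d = 0.5: √(125 × 0.25 / 3) = 3.227, power 0.893 (stated 0.89).
- d = 0.8: √(125 × 0.64 / 3) = 5.164, power 0.999 (stated 0.99).

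The stated figures therefore come from taking the couple as the cluster. The group is absent from the power calculation as well as from the model.

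**2. Count the randomized units.** Of the 128 couples randomized, 10 were allocated singly, leaving 118. If all 118 were in groups of two: 118/2 = 59, plus 10 = 69 units. In groups of four: 118/4 = 29.5, plus 10 = about 40 units. Groups of one would raise the count.

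**3. Add the group.** Let m be couples per group and ρ the correlation between people from different couples in one group; both are assumed. Take individual variance as 1. A couple mean then has variance (1 + 0.5)/2 = 0.75, and the true variance of the arm difference relative to the dyad-only variance is

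R = [1.5 + (2m − 2)ρ] / 1.5 = 1 + (m − 1)ρ/0.75.

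The true size of a nominal two-sided 5% test is 2·[1 − Φ(1.96/√R)]. For example, m = 3 and ρ = 0.05 give R = 1 + 2 × 0.05/0.75 = 1.133 and size 0.066.

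| Couples per group | ρ = 0.02 | ρ = 0.05 | ρ = 0.10 |
|---|---|---|---|
| 2 | R 1.027, size 0.053 | R 1.067, size 0.058 | R 1.133, size 0.066 |
| 3 | R 1.053, size 0.056 | R 1.133, size 0.066 | R 1.267, size 0.082 |
| 4 | R 1.080, size 0.059 | R 1.200, size 0.074 | R 1.400, size 0.098 |
| 6 (maximum) | R 1.133, size 0.066 | R 1.333, size 0.090 | R 1.667, size 0.129 |

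With m = 1, R = 1 and nothing changes.

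**4. Allow for the 10 single couples.** The table puts every couple in a group of m. With 10 of 128 couples single and the rest in groups of m, replace m by (10 + 118m)/128. For m = 4 this is 482/128 = 3.77, so at ρ = 0.10 R = 1 + 2.77 × 0.10/0.75 = 1.369 and the size is 0.094 instead of 0.098. Groups of one would lower it further by an unknown amount.

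**5. Power with the group included.** Multiply the variance by R and use 125/m − 2 degrees of freedom. Power for d = 0.5 falls from 0.893 to 0.880–0.847 for m = 2 and to 0.851–0.751 for m = 4 (ρ = 0.02 to 0.10).

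Steps 3–5 treat the effect as a difference in means of a continuous outcome at one time point. They indicate the order of magnitude for the growth-model terms and do not simulate that model.

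**The case against.** The strongest objection is that nothing in the article shows a positive correlation between unrelated couples, and several features would keep it small. Sessions 3 and 4 involve one couple at a time, and in 2GETHER the relationship agreement and prevention planning happen there. Couples who missed a group session could have a make-up session. After March 2020 the didactic content moved to self-paced videos. A reader might infer that every group shared about 6.5 hours together, but that figure is stated only for the in-person 2GETHER group sessions. All this stands: it limits the likely size of the correlation, but does not make it zero.

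Second, groups were hard to fill and some couples were randomized alone. For those couples the dyad is the correct level. This also stands, and it makes the six-couple row of the table remote.

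Third, the article adjusts for imbalances that randomization did not address. If the minimization factors are therefore left unadjusted, inference tends to be conservative, which could partly offset the inflation. That is possible but unquantified, and an accidental offset is no substitute for the right error term.

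Fourth, a fuller protocol or analysis plan may handle the group. But the article does not leave the level of treatment open. It names one, and that level conflicts with its own allocation section.

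A reader might also infer that the mediation bootstrap resamples the wrong unit. The article specifies a percentile bootstrap without a resampling unit, so no error is stated there.

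**Conclusion.** The described model does not match the described randomization for couples allocated in groups of two or more. That much follows from the text alone.

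It is tempting to go further and say that the standard errors are too small. The documents do not establish this, because it requires a positive between-couple correlation that they do not report. Under the assumptions in the working (within-couple correlation 0.5, groups of 2–4 couples, between-couple correlation 0.02–0.10), the true size of a nominal 5% test is about 0.053–0.098. It reaches 0.129 only if every group has six couples and the correlation is 0.10. At the smaller group sizes and correlations the inflation is modest. The comparison is between roughly 40–69 randomized units, or more with groups of one, and about 128 couples.

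The point merits correction before the final analysis because it touches a primary outcome and needs no new data.

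**What to change.** State that the unit of randomization is the session group. Then use one of two analyses:

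- Add the randomization group as a third level (participants within couples within groups), with treatment as a group-level predictor.
- More simply, keep the dyadic growth model and use cluster-robust variance at the group level with a small-sample correction.

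Couples randomized singly form their own cluster, or are assigned to the session group they attended; choose one rule in advance. The choice matters for the first 10 couples, who were randomized individually but whose first two sessions were designed as group sessions. Any mediation bootstrap should resample the same clusters.

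The change is to analysis wording only. Allocation and scheduling already define group membership, and follow-up was still under way according to Trial status. The cost is slightly wider intervals and fewer degrees of freedom. As a rough guide, units minus two gives 40 − 2 = 38 to 69 − 2 = 67, against 128 − 2 = 126 for couples, so the 5% critical value is about 2.02 to 2.00 instead of 1.98. The three-level model may estimate the group variance poorly with many small or single-couple groups. If it does not fit, the robust-variance option is preferable.

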### Trial objectives and hypotheses

The goal of the current study is to conduct an attention-matched randomized controlled trial (RCT) with a 12-month follow-up to assess the efficacy of 2GETHER in reducing HIV risk relative to a positive affect enhancement program for couples. We are recruiting a sample of young male couples living in Chicago and surrounding areas, who will complete intervention sessions face-to-face in a university setting. We make the following specific hypotheses:

H1: For our primary outcomes, we will observe greater reductions in indicators of HIV risk at 12 months post-intervention among participants randomized to 2GETHER relative to control, including reductions in (1) self-reported condomless anal sex with serodiscordant or unknown status partners and (2) urethral and rectal Chlamydia and Gonorrhea infections. In addition to these primary outcomes measured at the individual level, we anticipate significant improvement in self-reported partner relationship agreement concordance and reductions in the frequency of agreement breaks in 2GETHER relative to control. Finally, we hypothesize that indicators of relationship functioning (e.g., communication, satisfaction) will mediate intervention effects.

H2: With regard to secondary and exploratory outcomes, we will observe greater improvements in various aspects of the HIV continua of prevention and care at 12 months post-intervention among participants randomized to 2GETHER relative to control. For secondary outcomes, we expect to observe improvements in HIV testing uptake (among HIV-negative and unknown status participants) and antiretroviral medication adherence (among HIV-positive participants). Exploratory outcomes will be the uptake of and adherence to pre-exposure prophylaxis (PrEP) among HIV-negative and unknown status participants and reductions in viral load among HIV-positive participants.

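### The H1 mediation test relies on a lag alone to protect the non-randomized mediator-outcome path and, as described, gives baseline relationship functioning and baseline risk no role

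*Protocol article*

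**What the plan says.** All references are to the protocol article.

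- **Hypothesis** (Trial objectives and hypotheses, H1): "we hypothesize that indicators of relationship functioning (e.g., communication, satisfaction) will mediate intervention effects".
- **When it is tested** (Analyses of primary aims): "Indicators of relationship functioning will be tested as mediators of significant differences between the two study arms on the primary outcomes".
- **Model** (same section): "This is a parallel process approach where the mediator is treated as a lagged effect to maintain the temporal order of events". No lag length is given, and the text does not say whether the tested path links levels, slopes or both.
- **Test** (same section): "A percentile bootstrap test will be used to determine the indirect effect of treatment on the outcome through the lagged mediator".
- **Waves in the outcome growth models** (same section): "Data from all four of our follow-up surveys (3, 6, 9, and 12 months) will be incorporated into those growth models". Treatment condition is the only predictor named, and it acts on both intercept and slope.
- **The only covariate rule** (same section): "Imbalances in key stratification variables in baseline data that were not addressed via randomization will be adjusted for in the analyses of treatment effects". The variables screened for it are "baseline differences on prognostic variables, like age discordance and couple HIV status, the main study outcomes, and demographic variables". Relationship functioning is not named among them.
- **Data available** (Table 1): relationship satisfaction, self-reported communication and condomless anal sex are each measured at baseline and at 3, 6, 9 and 12 months.

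**The concern.** The arms are randomized; the level of relationship functioning within an arm is not. Men and couples who communicated better before the trial may also have had less risk before it, and may go on having less. A lagged mediator inherits that association, because a stable trait measured at an earlier wave is still the same trait. The rule on baseline imbalances does not help. It concerns differences between arms, whereas confounding of mediator and outcome is present even when the arms are perfectly balanced.

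The risk is realistic because 2GETHER is a package. Its sessions (Interventions section) combine communication training with HIV-prevention content, adherence counseling and a drafted relationship agreement, while PEONY by design avoids communication and sexual health negotiation. 2GETHER could lower risk through the prevention content and separately improve functioning. The mediation analysis exists to tell these routes apart, and a test that mixes stable differences into the indirect effect cannot do so reliably. What is at stake is the mechanism claim in H1, not the efficacy comparison.

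**Working it through.** **1. The plan's own figure.** The article gives no operating figure for mediation. Its power statement (125 dyads, couple ICC 0.5) can be reproduced with the two-arm cluster formula ncp = sqrt(J f² / (4·ICC + 4(1-ICC)/n)), with J = 125, n = 2 and J-2 degrees of freedom, assuming two-sided 5%.
- f = 0.5: sqrt(125 × 0.25 / 3) = 3.23, power 0.893 (stated 0.89).
- f = 0.8: sqrt(125 × 0.64 / 3) = 5.16, power 0.999 (stated 0.99).

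The figures agree, but they concern the arm difference and say nothing about the indirect effect.

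**2. Size of the spurious path, in algebra.** Assumptions: unit-variance measures, 60% of variance stable, correlation rho between the stable parts, and **no** effect of mediator on outcome. The mediator is the mean of 3 and 6 months, the outcome the mean of 9 and 12 months.
- Variance of each mean: 0.6 + 0.4/2 = 0.8. Covariance: 0.6·rho.
- Unadjusted path: b = 0.6·rho/0.8 = 0.75·rho. At rho = -0.4, b = -0.30. With a treatment effect on the mediator of 0.5 SD, the false indirect effect is 0.5 × (-0.30) = -0.15.
- Adjusted for baseline mediator and outcome, with r = 0.6·rho = -0.24: residual covariance r - (0.84r - r³)/(1 - r²) = -0.0407; residual mediator variance 0.8 - (0.36 - 0.2r²)/(1 - r²) = 0.430; b = -0.095. The false indirect effect is -0.047, about 68% smaller but not zero, because a single baseline measure contains error.

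**3. How often the test is misled on a level path.** Simulation with 125 dyads, couple ICC 0.5, 60% stable variance, a continuous outcome, a direct treatment effect of -0.5 SD, a true mediator effect of zero, and a 95% percentile bootstrap resampling dyads. There were 400 trials per setting (Monte Carlo error up to about 2.5 points).

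| Stable correlation | Mediator effect 0.3 SD: unadjusted / adjusted | Mediator effect 0.5 SD: unadjusted / adjusted |
|---|---|---|
| 0 | 4% / 6% | 5.5% / 7% |
| -0.1 | 12% / 5% | 20% / 5% |
| -0.2 | 35% / 10% | 55% / 12% |
| -0.3 | 53% / 17% | 83% / 20% |
| -0.4 | 61% / 26% | 94% / 34% |

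**4. Allowing for the significance condition.** Mediation is tested only after a significant arm difference. Dividing the joint rate (significant arm difference and false mediation) by the rate of significant arm differences, unadjusted:
- rho -0.1: 0.115/0.975 = 12% (0.3 SD) and 0.172/0.930 = 18% (0.5 SD).
- rho -0.2, 0.3 SD: 0.328/0.938 = 35%.
- rho -0.4, 0.5 SD: 0.898/0.942 = 95%.

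A further simulation, also conditional on a significant arm difference, gave 45-99% unadjusted against 12-45% adjusted for -0.2 to -0.4, and 14-22% against about 8% at -0.1. Taking all runs together, the ranges are about 35-99% against 10-45%, and 12-22% against 5-8%.

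If treatment has **no** effect on risk, the condition is met in only about 4-6% of trials, and false mediation together with a significant arm difference occurs in 2.5-4%.

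**5. Slope-on-slope path.** A constant trait cancels out of a slope, so the covariance in step 2 vanishes. With a stable correlation of -0.4 and a treatment effect on the mediator that builds linearly to 0.5 or 1.0 by 12 months, false mediation occurs in 1% and 7% of trials, with or without baseline covariates. Correlated changes over time (-0.6, no stable correlation) give 7% and 17% unadjusted, and 6.5% and 15.5% adjusted. Baseline covariates do nothing for that kind of confounding.

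**The case against.** The strongest reply is that this is a condensed article. It gives mediation one short paragraph, defers to a cited method, and says that the full protocol is available on request. Covariates may be listed there, and the article does not state that the path is unadjusted. The sentence on the four follow-up surveys belongs to the outcome models and does not expressly exclude baseline. This stands as a limit on the claim. A reader should not infer that the investigators decided against baseline adjustment. What remains is that the article does describe a specification (waves, predictor, lag, test and a covariate rule), and within it the lag is the only protection for this path.

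Second, a parallel-process model may test slopes against slopes, which removes stable differences. This also stands, and the article does not say which path is meant. However, follow-up is counted from the end of the intervention. Any gain in functioning reached by 3 months lies in the level rather than in the later slope, so a slope-only test could miss it. In the simulations with a full effect by 3 months, the slope path was significant in at most 0.5% of trials.

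Third, the significance condition limits the harm. This is correct where 2GETHER has no effect on risk. It does not help where 2GETHER lowers risk by another route, which is the case that mediation analysis is meant to sort out.

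A reader might also infer that men will be resampled individually, breaking up couples. The text does not say so, and the preceding paragraph adopts multilevel models because of the dyadic data. No such claim is made here.

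**Conclusion.** The point holds in a limited form. As described, the mediation test protects a non-randomized path by temporal order alone, and gives no role to two baseline measures that the trial already collects. The indirect effect can therefore be biased toward mediation. The size cannot be fixed from the document. The false-positive ranges above need three things together: a significant arm difference on risk, a real effect of 2GETHER on the mediator, and a level-on-level path. They also rest on assumed stable correlations, an assumed stable share of variance and a continuous stand-in for the behavioral outcome.

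The tempting stronger reading is that the test will usually declare mediation whenever 2GETHER improves relationship functioning. The documents do not support it. They give no correlation between functioning and risk, they restrict when mediation is tested, and they leave open a slope path that stable differences barely affect. The efficacy conclusions on the primary outcomes are not touched.

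**What to change.** In the mediation paragraph of Analyses of primary aims, or in the analysis plan:

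- Include the baseline value of the mediator, the baseline value of the outcome and the minimization factors (couple age discordance, couple HIV status, baseline STI) as covariates in **both** the mediator and the outcome equations.
- State whether the indirect effect is defined on levels, slopes or both, since the exposure to bias depends on it.
- Report the indirect effect as conditional on no remaining mediator-outcome confounding, with a sensitivity analysis showing how large a residual correlation would remove it. This is needed because adjustment left 10-45% false mediation at stable correlations of -0.2 to -0.4, and does not address confounding that arises after baseline.

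**Cost:** wording and some analysis time, with no new data collection. The models gain a few parameters and the interval for the indirect effect may widen. Baseline STI is missing for couples assessed during the 2020 gap in specimen collection, so its use as a covariate needs a stated rule for those couples.
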